#### Study population: inclusion criteria (most important in- and exclusion criteria)

##### Exposed group

- Workplaces where loads on hands and arms exceed the action limit of the HAL TLV (Hand Activity Level Threshold Limit Values; Hoehne-Hückstädt et al., 2007). These limits from the American Conference of Governmental Industrial Hygienists were developed with the goal of preventing work-related illnesses.
- Workload analysis: a daily repetitive strain of at least five hours on one or both hands and at least four days a week with a strain intensity above the action limit of the HAL TLV (Kapellusch et al., 2018).
- Employment: a minimum of one-year employment to above described workplaces at the time of study inclusion.
- Musculoskeletal pain: the study population should suffer from varying degrees of musculoskeletal pain in the elbow/forearm/hand-area, which will be assessed using the Cornell Musculoskeletal Discomfort Questionnaire (Kreuzfeld et al., 2016). Ideally, the population covers the whole range from no pain to very severe pain. However, subjects have to be able to work.

##### Unexposed control group

- Workplaces without physical loads based on the basic screening tool to detect physical stress at work (BAuA, 2022, p. 1) as provided by the Federal Institute for Occupational Safety and Health (*Bundesanstalt für Arbeitsschutz und Arbeitsmedizin*; BAuA), such as office work.
- Employment: a minimum of one-year employment to above described workloads at the time of study inclusion.
- Musculoskeletal pain: the study population should not suffer from musculoskeletal pain within the last four weeks, which will be assessed using the Cornell Musculoskeletal Discomfort Questionnaire (Kreuzfeld et al., 2016).

#### Study population: exclusion criteria

- Status after accident and/or systemic diseases that affect joints or muscles and/or are associated with acute and chronic inflammations.
- Exposed group: Musculoskeletal pain that is not localized in the elbow/forearm/hand-area and that is equally or more severe than in the elbow/forearm/hand-area examined in the current study, as assessed by the Cornell Musculoskeletal Discomfort Questionnaire (Kreuzfeld et al., 2016).
- Unexposed control group: Relevant physical demands in the workplace according to the basic screening tool to detect physical stress at work (BAuA, 2022) at study inclusion.
- Relative and absolute contraindications for repeated blood sampling, such as: fear of blood sampling (relative), taking anticoagulants (absolute), few suitable veins that should only be used for therapeutic interventions (absolute).

#### Study procedure (work packages)

1. Selection and recruitment of study population (~3 months; underestimated, delayed).
2. Preparation of measurement procedures (~5 months).
3. Carrying out the measurements including data preparation (~11 months).
4. Data analysis (~4 months).
5. Publication and external follow-up funding (~3 months).

#### Study outcomes

Several methods are performed, with each having its own outcome(s):

- Exposure at work
  - Hand activity level
  - Assessment of load in manual work
- Specified medical examination with medical anamnesis
- Pain provocation
  - Pain triggering
  - Pressure pain thresholds on epicondyles and carpal tunnel
- Rating of perceived pain using a 0-10 numeric rating scale
  - Pain intensity at night, during the working week (min. and max.), current pain
- Inflammation parameters in the blood by taking a 2-weekly blood sample
  - Level and variability of the concentration of CRP, IL-6 and IL-1 $\beta$

|                           |                                       |
|---------------------------|---------------------------------------|
| Planning                  |                                       |
| Total study duration      | 30 months (i.e., 2.5 years)           |
| Individual study duration | Up to 18 weeks (i.e., about 4 months) |

## I Abstract

**Background:** In animal models, sustained repetitive stress to the forepaws resulted in chronic inflammatory responses in the musculoskeletal system due to lack of recovery and adaptation. Such evidence is lacking in workers with occupational musculoskeletal exposures.

**Objectives:** To investigate which biomarkers (e.g., IL6, CRP in blood) are suitable and how they are best determined methodologically.

**Methods/Design:** Inflammatory biomarkers (CRP, IL-6, IL-1 $\beta$  as potential markers of inflammation) will be determined over 11 to 17 weeks in 20 individuals (half men) (exposed group) with high physical workloads and varying degrees of musculoskeletal pain in the hand-arm system. In addition, 20 individuals (half men) (unexposed control group) with low physical workload and no musculoskeletal pain in the hand-arm-system will be recruited. The biomarkers will be taken by blood samples (~11-16 ml per sample), musculoskeletal pain will be assessed using a visual analogue scale, and work exposures and clinical signs of chronic musculoskeletal disorders will be monitored as well.

**Analysis within the exposed group and unexposed control group:** Analyzed will be a) which biomarkers need to be collected how often to obtain reliable values and b) the magnitude of correlations between pain frequency/intensity and inflammatory marker concentration. Additionally, clinical signs of chronic musculoskeletal disorders will be correlated with inflammatory marker concentration as well.

**Analysis between the exposed group and unexposed control group:** The level of inflammatory marker concentration will be compared between groups.

The results of this preliminary study will be used to apply for funding of a cohort study to investigate causal relationships between chronic inflammation and persistent musculoskeletal complaints in physically exposed workers. Such evidence and effects of recovery-effective breaks would enable new approaches in preventing work-related musculoskeletal disorders, which is urgently needed in view of the high economic burden of work-related musculoskeletal disorders.

**Trial registration:** The study is registered in the German Clinical Trials Register (DRKS00031872).

**Data protection:** The physically and digitally collected data will be numerically pseudonymized by assigning a randomly generated, two-digit identification number to the examined participant to maintain confidentiality.

## II Keywords

Inflammation; work-related musculoskeletal disorders; musculoskeletal pain, physical work

## 1 Abbreviations

|               |                                                                                                           |
|---------------|-----------------------------------------------------------------------------------------------------------|
| AKF           | Applied Clinical Research [Angewandte Klinische Forschung]                                                |
| BAuA          | Federal Institute for Occupational Safety and Health [Bundesanstalt für Arbeitsschutz und Arbeitsmedizin] |
| CRP           | C-reactive protein                                                                                        |
| CTGF          | Connective tissue growth factor                                                                           |
| DFG           | German Research Foundation [Deutsche Forschungsgemeinschaft]                                              |
| DRKS          | German Clinical Trials Register [Deutsches Register Klinischer Studien]                                   |
| ELISA         | Enzyme-linked immunosorbent assay                                                                         |
| HAL TLV       | Hand Activity Level Threshold Limit Values                                                                |
| IASV          | Institute of Occupational and Social Medicine and Health Services Research                                |
| IL-1 $\beta$  | Interleukin-1 $\beta$                                                                                     |
| IL-10         | Interleukin-10                                                                                            |
| IL-6          | Interleukin-6                                                                                             |
| MMP2          | Matrix metalloproteinase 2                                                                                |
| MSD           | Musculoskeletal disorder                                                                                  |
| NMI           | Natural science and Medical Institute                                                                     |
| PPT           | Pressure pain threshold                                                                                   |
| TGFB1         | Transforming growth factor beta 1                                                                         |
| TNF- $\alpha$ | Tumor necrosis factor alpha                                                                               |
| VAS           | Visual analogue scale                                                                                     |
| ZKS           | Center of Clinical Trials [Zentrum für klinische Studien]                                                 |

## 2 State of the art

### 2.1 Epidemiology of work-related musculoskeletal disorders

Musculoskeletal disorders (MSDs) are one of the most common causes of work absenteeism (Burton & Kendall, 2014). In stressful work situations, about half of the working population suffers from recurrent pain in the musculoskeletal system (Läubli, 2014). Several specific diseases of the back, neck, knee and others are recognized as occupational diseases in Germany (BAuA, 2021). The majority of MSDs in the working force are judged to be work-related, meaning that workload is considered an important sub-cause in a multi-causal disease process (Liebers & Caffier, 2009). Important stress factors are high force demands (lifting and carrying), repetitive activities, and awkward body postures, which are required during a substantial part of working hours (Dick et al., 2020; Kilbom et al., 1996).

### 2.2 Occupational physiological findings on work-related musculoskeletal disorders

Ergonomic work design is based on the so-called Stress-Strain Concept (Rohmert, 1986), where “stress” stands for the objective work characteristics and “strain” for all physiological and psychological reactions in the workers. A central principle of ergonomic work design is that the work requirements do not lead to a strain that exceeds long-term performance. In addition to e.g. adapting working heights to body size, excessive stress and fatigue must be prevented by means of work breaks.

Occupational health and safety enforcement authorities worldwide use standardized assessment procedures to prevent work-related MSDs. However, the preventive effect of such work design measures is insufficient, and the question arises as to whether previously ignored stress factors are significant for the occurrence of MSDs (Forde et al., 2002; Westgaard & Winkel, 1997).

We postulate, supported by publications of other authors, that too little attention has been paid to recovery in previous analyses. We know from the field of competitive sports that training can lead to an enormous increase in performance, i.e., that heavy loads per se do not have to be a health hazard. In sports, however, the so-called overtraining is a feared condition, because then the training efforts do not lead to a further increase in performance but rather to a decrease. The phenomenon of overtraining can occur when there is a combination of insufficient recovery time and high training intensity at the same time. Recovery has hardly been addressed in the occupational physiology and occupational medicine literature, and it may be of particular importance for the chronicity of work-related MSDs, especially in the modern workplace (Sjøgaard & Sjøgaard, 2014). This statement will be explained in the next three chapters (see 2.3, 2.4, 2.5).

### 2.3 Rat model

The research group of Barr and Barbe (2002) developed a rat model to study the consequences of repetitive voluntary movements. Both the force demand and the frequency of the movements can be influenced in a standardized manner. The primary interest was studying inflammatory and degenerative processes in the directly affected muscles, tendons, nerves, and bones of a forepaw, but from the beginning attention was also given to a systemic response and neurological reorganization at the levels of the spinal cord and the brain. The consequences of such repetitive, powerful, voluntary movements with the forepaw can be summarized as follows (Barbe et al., 2013):

1. Histological changes: tendon (disrupted fibrils, ruptures of collagen fibers); muscle (atrophy); articular cartilage (changes in matrix, cysts); nerves (axon and myelin damage).
2. Inflammatory signs: increased macrophages and cytokines in all tissues involved; increased cytokines in blood serum; increased substance P and inflammation in the spinal cord.
3. Fibrosis/degeneration: detectable in median nerve, tendons and muscles; degeneration of articular cartilage; resorption of bone and reduced quality of bone.

4. Functional decrements: pain behavior; reduced grip strength; reduced performance in target movements.

On the question of which serum inflammatory indicators were at least statistically correlated with decreases in grip strength in rats, Gao and colleagues (2013) reported significant inverse correlations for IL-6, MMP2, TGFB1, and TNF- $\alpha$ . From the analyses, the study concluded: "Serum TNF- $\alpha$ , IL-6, TGFB1, CTGF and MMP2 may serve as serum biomarkers of work-related musculoskeletal disorders, although further studies in humans are needed."

## 2.4 Inflammation and regeneration in muscle and tendons

### 2.4.1 Muscles

Physical stress induces an acute inflammatory response in the muscles and systemically. In this process, inflammatory mediators are released by muscle cells, but also by other tissues and organs, which can be detected in the blood circulation. The cytokines released by muscle cells are also called "myokines", although most are not muscle-specific, but are also produced by other tissues and organs. Best studied in this context are the cytokines IL-1 $\beta$ , TNF- $\alpha$ , and especially IL-6, whose concentration in serum can briefly increase many times after exercise. In addition, the CRP (C-reactive protein) value is frequently determined as a routine laboratory parameter. Interestingly, individuals adapted to exercise usually have lower resting concentrations of these inflammatory mediators compared to untrained controls. Various results indicate that the tightly timed, well-controlled inflammatory response immediately following exercise is important for muscle tissue regeneration and adaptation, whereas permanently elevated inflammatory parameters, as found in many chronic disease conditions but presumably also in lack of regeneration, are rather counterproductive (Fedewa et al., 2017; Hoffmann & Weigert, 2017).

### 2.4.1 Tendons

Inflammatory mediators also appear to play an important role in the regeneration and adaptation processes of tendons. The authors of a recent review (Morita et al., 2017) concluded that, similar to skeletal muscle, the cytokines IL-1 $\beta$ , IL-6, IL-10, and TNF- $\alpha$  may be of particular importance. In addition, there is evidence of crosstalk between muscle and tendon (Aicale et al., 2018). Finally, it is likely that similar to skeletal muscle, acute inflammatory processes might be important for regeneration and adaptation, and that more or less chronic inflammation, triggered e.g. by frequent exercise with only short recovery intervals, might be counterproductive (D'Addona et al., 2017).

## 2.5 Conclusions

With reference to occupational exposures, we developed the following model from the findings presented above (**Figure 1**): in the case of work-related exposures, the inflammation and regeneration phase after high levels of stress is often disrupted by subsequent workloads, so that instead of recovery and strengthening of the tissues, chronic inflammation develops. This chronic inflammation leads to fibrosis of the affected tissues and is accompanied by persistent or recurrent pain (Barbe & Barr, 2006). In order to be able to clarify this postulated relationship in a future epidemiological long-term study (cohort study), this preliminary study is intended to clarify open methodological questions. In general, the clarification of the postulated relationship is important, as it can be used in the long term to develop meaningful stress-recovery concepts for occupations with different physical demands, through which the risk of work-associated MSDs can be reduced. A look at the analyses of health insurance statistics published by Liebers and Caffier (2009) show that in occupational groups whose activities are characterized by high force demands and repetition, there is a more than fourfold increase in the risk of, for example, tendinitis/tenosynovitis of the elbow. Although the analyses of Liebers and colleagues cannot reveal causal relationships, they show that the preventive effect of current work design measures is not sufficient and that there is a high need for research and practice here. In addition, depending on the results of the preliminary and (if

applicable) the future cohort study, selected biomarkers could be used in occupational health check-ups for early detection of individual workers suffering from work-related overstrain.

[figure not shown]

**FIGURE 1.** MODEL OF THE RELATIONSHIP BETWEEN WORKLOAD, CHRONIC INFLAMMATION, AND MUSCULOSKELETAL DISORDERS. BASED ON THE FUNDAMENTALS OF BARBE AND BARR (2006) AND BARBE ET AL. (2013).

### 3 Study objectives

The results of the animal experiments (cf. 2.3) published so far are to be verified in humans. To this end, a preparatory methodological study is to be carried out in order to clarify open methodological aspects for the subsequent implementation of a long-term study (cohort of occupationally exposed persons). Against the background depicted in 2.3, 2.4, and 2.5, we will focus on CRP, IL-6 and IL-1 $\beta$  as potential markers of inflammation. In the proposed preliminary study, we have two study objectives:

1. Assess the reliability of inflammation parameters by repeated measurements.
2. Conduct a cross-sectional exploratory investigation to determine whether clearly significant correlations between signs of chronic inflammation (in the blood serum) and musculoskeletal (upper-extremity) pain can be demonstrated in occupationally stressed subjects.
3. Compare signs of chronic inflammation (in the blood serum) between individuals exposed to high physical workload in the upper extremities and individuals with low physical workload.

A subsequent long-term study (not part of this ethics proposal) will then show whether the corresponding correlations can be understood as causal mechanisms. In this follow-up project, newcomers to stressful occupations will be followed for one to two years. A causal chain would consist of a chronic inflammatory condition following acute epicondylitis if recurring stresses occur during the healing phase. Subsequently, chronic recurrent subclinical complaints would persist. To elaborate the design of a subsequent long-term study, results on the following aspects are expected:

- Reliability/repeatability of the measured values, especially the parameters obtained from the blood serum, in order to determine the parameters suitable for the long-term study and to determine the length of the time intervals between measurement repetitions.
- Relationship between signs of chronic inflammation and pain frequency/intensity and intra- and interindividual variability of measurement parameters for sample size calculation for the follow-up study.

- Exposure assessment by observational methods: evaluation of the literature (e.g., Klußmann et al., 2010; Takala et al., 2010) and selection and testing of two methods in the field to identify the most appropriate method for the follow-up study (practicability).
- Comparison of two blood analysis methods that both determine inflammatory indicators related to (occupational) physical stress.

### 3.1 Primary objective

Reliability of measurement parameters for inflammation and musculoskeletal pain at consistent high workloads over time.

### 3.2 Secondary objectives

- Clear correlations between inflammatory parameters (biomarkers) and persistent local musculoskeletal symptoms (duration and intensity) during occupational stress.
- Correlation between inflammatory parameters (biomarkers) and clinical findings of chronic MSE at the elbow/forearm/hand-area.
- Comparison of inflammatory biomarker concentration between individuals exposed to high and low physical workload.

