### 4.1 Study population

The study population consists of 20 individuals exposed to high physical workload (exposed group) of the upper extremity and 20 individuals exposed (unexposed control group) to low physical workload. The exposed group is in the focus of this research project and should consist of ten women and ten men with highly stressful occupational activities of the hands (e.g., upholsterer as profession), who report minor to severe recurrent pain in the elbow/forearm/hand-area. Participants of the unexposed control group should also consist of 10 women and 10 men but with only low exposure to physical workload and no musculoskeletal pain. Participation is on a voluntarily basis, meaning that the subject is always free to stop participation in the study without justification.

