##### Exposed group

- Workplaces where loads on hands and arms exceed the action limit of the HAL TLV (Hand Activity Level Threshold Limit Values; Hoehne-Hückstädt et al., 2007). These limits from the American Conference of Governmental Industrial Hygienists were developed with the goal of preventing work-related illnesses.
- Workload analysis: a daily repetitive strain of at least five hours on one or both hands and at least four days a week with a strain intensity above the action limit of the HAL TLV (Kapellusch et al., 2018).
- Employment: a minimum of one-year employment to above described workplaces at the time of study inclusion.
- Musculoskeletal pain: the study population should suffer from varying degrees of musculoskeletal pain in the elbow/forearm/hand-area, which will be assessed using the Cornell Musculoskeletal Discomfort Questionnaire (Kreuzfeld et al., 2016). Ideally, the population covers the whole range from no pain to very severe pain. However, subjects have to be able to work.

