##### Unexposed control group

- Workplaces without physical loads based on the basic screening tool to detect physical stress at work (BAuA, 2022, p. 1) as provided by the Federal Institute for Occupational Safety and Health (*Bundesanstalt für Arbeitsschutz und Arbeitsmedizin*; BAuA), such as office work.
- Employment: a minimum of one-year employment to above described workloads at the time of study inclusion.
- Musculoskeletal pain: the study population should not suffer from musculoskeletal pain within the last four weeks, which will be assessed using the Cornell Musculoskeletal Discomfort Questionnaire (Kreuzfeld et al., 2016).

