## 6.2 General medical anamnesis and examination for inclusion

The screening at study inclusion consists of three steps. First, the general medical anamnesis and examination are performed by a physician at study inclusion (T0). The medical anamnesis is an individually adjusted checklist by the occupational and medical outpatient clinic of the IASV and is based on the original UKT medical anamnesis checklist. The specified medical examination is performed according to the guidelines for physicians as provided and developed by the German Social Accident Insurance (DGUV, 2017). The medical examination indicates the mobility of body joints based on the neutral-zero-method (Ryf & Weymann, 1995).

Second, eligibility criteria are checked (cf. **4.4.2**), demographic data are collected (body weight, length, age, gender, activity level, etc.) and the Cornell Musculoskeletal Discomfort Questionnaire (CMDQ; Kreuzfeld et al., 2016) is filled out. The CMDQ is used to map whether the elbow/forearm/hand-area is the region where the main musculoskeletal pain is perceived. The questionnaire showed a good validity (kappa value 0.38-1.00; Spearman's correlation coefficient 0.40-1.00; Kreuzfeld et al., 2016). It also showed satisfactory internal consistency (Cronbach's alpha 0.75-0.82) and medium to substantial test-retest reliability (Spearman rank correlation coefficient 0.56-0.72; Kreuzfeld et al., 2016).

Finally, a blood sample (~11 ml) is taken from the participant in order to retrieve a general blood picture (i.e. differential blood analysis) and verify that participants are free from acute infection.

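### Eligibility makes the two groups differ in pain as well as workload, so the third secondary objective cannot be read as a workload contrast

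*Protocol*

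**What the plan says.** **The objective.** Protocol Section 3.2 (also the synopsis, and item 3 of Section 3) names a "Comparison of inflammatory biomarker concentration between individuals exposed to high and low physical workload". Workload is the only trait that defines the groups there.

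**Controls.** Section 4.4.1 requires that "the study population should not suffer from musculoskeletal pain within the last four weeks". Section 4.1 likewise describes controls as similar in number and sex "but with only low exposure to physical workload and no musculoskeletal pain".

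**Exposed workers.** Section 4.1 describes workers "who report minor to severe recurrent pain in the elbow/forearm/hand-area". The inclusion criterion in Section 4.4.1 asks for varying degrees of pain and adds: "Ideally, the population covers the whole range from no pain to very severe pain". It sets no number or share of pain-free exposed workers.

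**Correlation.** The abstract lists "the magnitude of correlations between pain frequency/intensity and inflammatory marker concentration" under a heading that covers analysis within both groups. Section 3 confines this question to occupationally stressed subjects, and Section 4.5 bases it on the 20 exposed subjects.

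**Caveat.** Section 5.2.4 says that effects of different exposure levels cannot be tested, because the highly exposed sample is small. It keeps a general comparison with controls to help judge the potential of a later long-term study.

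**The concern.** Controls are chosen on two traits at once, and under Section 4.1 the exposed group is the opposite on both. The study's main correlation question is whether biomarkers track pain. If they do, the groups will differ even when workload has no effect of its own. A reader who takes the objective at its word would credit that difference to workload, and the comparison is meant to inform the case for a cohort study.

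The mixture arises at recruitment. If few or no pain-free exposed workers are enrolled, later analysis has little or no overlap in pain to work with. That makes it a matter for the protocol and not only for an analysis plan.

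The control-group correlation raises a related problem: a correlation with pain needs people whose pain differs, and controls are selected to have none at entry.

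**Working it through.** **1. Pain at entry, by section**

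| Source | Exposed | Controls |
|---|---|---|
| Section 4.1 | minor to severe recurrent pain | no pain |
| Section 4.4.1 | varying degrees; no pain included only as an ideal | no pain in the last four weeks |
| Section 3.2 (objective) | high workload; pain not mentioned | low workload; pain not mentioned |

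Under Section 4.1 the groups do not overlap in pain at entry. Under Section 4.4.1 they may overlap, but nothing assures it. The two sections disagree on whether a pain-free exposed worker belongs in the study.

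**2. The protocol's own figure.** Section 4.5 gives 0.38 as the significance limit for Spearman's rho with 20 subjects and α = 10%. Critical value = t/√(t² + n − 2), with n = 20 and two-sided 10%, gives 0.378. 0.38² = 0.144, or about 15% of variance. Both figures reproduce. Note that 0.38 is a significance limit, not an expected effect.

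**3. How large a difference pain alone could produce.** The inputs below are assumptions, apart from 20 per group (Section 4.1) and the value 0.38 (Section 4.5):
- true workload effect zero;
- exposed pain normal with mean 3–5 and SD 2–2.5, controls at 0;
- biomarker = rho × pain/SD(pain) + √(1 − rho²) × noise, so its SD in the exposed is 1;
- two-sided Welch test.

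Expected difference in SD units = rho × mean/SD(pain):

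| rho | Mean, SD of pain | Difference | Significant at 5% | at 10% |
|---|---|---|---|---|
| 0.38 | 3, 2.5 | 0.38 × 3/2.5 = 0.46 | 31% | 43% |
| 0.38 | 4, 2.5 | 0.38 × 4/2.5 = 0.61 | 49% | 62% |
| 0.38 | 5, 2.5 | 0.38 × 5/2.5 = 0.76 | 68% | 79% |
| 0.38 | 5, 2 | 0.38 × 5/2 = 0.95 | 86% | 92% |
| 0.2 | 3, 2.5 (lowest) | 0.2 × 3/2.5 = 0.24 | 11% | 19% |
| 0.2 | 5, 2 (highest) | 0.2 × 5/2 = 0.50 | 35% | 48% |

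The percentages are simulated and carry an error of about one point.

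**4. Dependence on pain-free exposed workers.** This is a separate simulation: pain uniform on 1–8 apart from a pain-free share, correlation 0.38 within the exposed, Mann–Whitney test at two-sided 10%, no workload effect. With 0%, 10%, 25% and 50% of exposed workers pain-free, the comparison is significant in about 76%, 58%, 41% and 24% of studies, against a nominal 10%.

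**5. Correlation within controls.** If all 20 controls stay at 0, Spearman's rho is undefined. If 1, 2 or 4 of the 20 report a pain score of 1–2 during follow-up, the chance of detection at the exposed-group slope is about 0%, 12% or 15% at the 10% level. It is about 50% in the exposed group.

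**The case against.** **No causal claim is made.** The objective says only that concentrations are compared. Section 3 leaves causality to a later study of newcomers to stressful jobs, and the abstract does likewise. This stands: a reader might infer that the protocol presents the contrast as proof that workload raises inflammation, and it does not. But the label still names workload alone, and the caveat in Section 5.2.4 rests on the small exposed sample, not on pain.

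**The simulation reverses the protocol's model.** Section 2.5 has workload leading to inflammation, with pain accompanying the result. Pain driving the biomarker is a device for illustration. This stands as a limit on the figures. Selecting on pain can still bias the contrast if pain is the consequence.

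**Contrasting extremes is legitimate in a preliminary study.** Agreed, provided that the contrast is named as such.

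**Absolute readings go too far.** One might conclude that workload and pain can never be separated, or that controls will show no pain variation at all. Section 4.4.1 permits some pain-free exposed workers. The control criterion covers only the four weeks before entry, while pain is rated from T1 to T9 (Section 6.3). The supportable wording is that overlap is not assured and that controls will have almost no variation.

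**The control correlation is a loose abstract heading** that also covers reliability. Probably so, but it conflicts with Sections 3 and 4.5. No passage plans to pool the groups.

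**Covariate adjustment belongs in an analysis plan.** Agreed; its absence here is no finding.

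**Conclusion.** The point holds as a matter of labelling and eligibility. The groups differ by design in pain as well as workload, so the third secondary objective does not isolate workload, and the protocol nowhere says so. Sections 4.1 and 4.4.1 conflict on pain-free exposed workers. The abstract's correlation within controls would be undefined or nearly uninformative.

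The size is illustrative. Pain alone could give about 0.46–0.95 SD at rho 0.38 (significant in 31–86% of studies at 5% and 43–92% at 10%), but only 11–35% and 19–48% at rho 0.2. The rates fall as more exposed workers are pain-free. The pain distributions, the two correlations as effect sizes and the pain-only model are all assumptions.

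This should be fixed but is not critical. The primary reliability objective and the exposed-group correlation on which the sample size rests are untouched.

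**What to change.** 1. Restate the objective (synopsis, Sections 3 and 3.2) as a comparison of exposed workers with varying arm pain against unexposed pain-free workers, and state that it does not isolate workload.
2. Reconcile Sections 4.1 and 4.4.1 so that it is clear whether exposed workers without arm pain are eligible. If they are, report as a supportive analysis the contrast of exposed workers with no or minimal pain against controls, noting that this subgroup is small and its size is not assured.
3. Limit the abstract's pain–biomarker correlation to the exposed group.

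Adjustment for sex, age, BMI and activity level is an optional supplement. The data are collected at T0 (Section 6.2), and Section 2.4.1 itself notes that "individuals adapted to exercise usually have lower resting concentrations of these inflammatory mediators compared to untrained controls". It would not remove the mixing of pain with workload.

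The cost is wording, one supportive analysis and a more modest claim. The sample size does not change.
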